## Abstract

**Background:**

Poor nutrition and inadequate physical activity are key contributors to rising chronic disease rates across the United States. It is well-documented that neighborhood built environments play an important role in shaping these modifiable health behaviors. Agriculturally-integrated neighborhoods (“agrihoods”) offer a relatively new and promising approach to health-promoting residential design and development. Centered around a working farm, agrihoods are designed to connect residents with fresh foods and outdoor spaces that encourage physical activity. However, no rigorous or longitudinal evaluations of their impact on resident health have been conducted to date. We detail the protocol for a naturalistic study that aims to (1) assess short-term changes in dietary intake, physical activity, cardiometabolic health indicators, and social connectedness among agrihood and matched comparison residents; (2) document time use with and preferences for agrihood design features; and (3) examine agrihood economic benefits.

**Methods:**

This mixed-methods, quasi-experimental study will last approximately 6 months including assessment at three timepoints (baseline, 3 months, 6 months). Agrihood participants will be new adult residents in an agrihood residential development (Richmond, TX), while comparison participants will be adults currently residing in a nearby residential development (Katy, TX). All participants will complete three 30-min online surveys, including items to produce geospatial data; agrihood participants will complete two additional 30-min in-person health assessments and three timepoints of accelerometer wear on 7 consecutive days, with a subsample completing three 30-min online dietary recalls. Data will be collected by trained staff, and Difference-in-Differences (DiD) generalized linear mixed-effects models will examine longitudinal change and its interaction with participant groups. The economic analysis will account for break-even time, farmer compensation, maintenance costs, and public incentive programs.

**Discussion:**

This will be the first study to examine a longitudinal cohort of new agrihood residents compared to a master planned residential development to understand the use and health impacts of agrihood living. Our data-driven design, including biological data collection, device-captured physical activity, and validated self-report measures, can pave the way for future research, policy and philanthropic initiatives to adapt and scale models for developments that promote environmental and economic growth, and improve human health and wellbeing.

**Clinical trial registration:**

https://clinicaltrials.gov/study/NCT06950775, Identifier NCT06950775.

## Introduction

Poor nutrition and inadequate physical activity are prevalent in many communities across the United States, contributing to rising rates of chronic diseases such as obesity, diabetes, heart disease, and certain cancers (1–3). Consuming a healthy diet and being physically active are not only important for preventing these health conditions but also for managing and, in some cases, improving them (1). While socioeconomic disparities significantly influence access to healthy food and safe places to be active, a range of societal, environmental, and policy factors shape modifiable health behaviors across all socioeconomic groups (4). In fact, neighborhood built environments have been linked to outdoor activity and diet quality as well as social connection (5–10), sometimes regardless of socioeconomic status (11), pointing to an opportunity to improve health on a broader scale through the intentional design of neighborhoods that foster walkability, healthy food retail and agriculture, and social interaction.

Over the last decade, agriculturally-integrated neighborhoods called “agrihoods” have risen in popularity and present a promising avenue for positioning health at the center of land-use development (11). While there are no established definitions or required components to be considered an agrihood, these neighborhoods typically consist of residences ranging from apartments and condos to attached and single-family homes constructed around a working farm. There is often particular emphasis placed on environmental sustainability (i.e., regenerative farming practices, reduced personal vehicle use and food transportation needs) and community engagement (i.e., community-led gardens and farmers markets, educational and recreational events). Agrihoods can also help support local economies through job creation for farming, food production, and community-based enterprises (12). Property values in agrihoods tend to be higher due to the unique appeal of living close to green spaces and farms, attracting buyers seeking a healthier, eco-friendly lifestyle (13, 14). Additionally, these communities can boost tourism and local commerce by hosting farm-to-table events, farmers’ markets, and educational programs, creating a ripple effect of economic growth and resilience throughout the region (12, 15, 16).

Currently, it is believed that more than 200 agrihoods are planned or developed in the United States, spanning nearly 30 states. Despite this, a recent review by our research team found limited peer-reviewed published literature on agrihoods, and none that rigorously or longitudinally evaluate their impact on health (17). Impact evaluations, especially those using validated measures, are needed to better understand agrihood characteristics, community use of and engagement with resources and agriculture by agrihood residents, changes to agrihood residents’ health behaviors, and community involvement in the design and maintenance of agrihood environmental features and agricultural production (17). Doing so could help inform the design of replicable agrihood models that can be tailored to meet the needs of various populations and settings.

Therefore, we detail the protocol for a naturalistic study, referred to as the *Neighborhood & Health Study*, which aims to assess the impact of relocating to an agrihood on health and economic outcomes among residents of a newly developed agrihood neighborhood in Fort Bend County, Texas, compared to a geographically and socio-demographically matched non-agriculturally-integrated, master-planned neighborhood, located 23 miles away (by car) in neighboring Harris County, Texas. Given the need for evaluations of agrihood impacts over time and in various settings, we present our scalable methodology for (1) assessing short-term changes in dietary intake, physical activity, cardiometabolic health indicators, and social connectedness among agrihood residents compared to those of a matched master-planned neighborhood that is not agriculturally-integrated; (2) documenting resource utilization and time use with and preferences for built and nature design features of the agrihood; and (3) examining economic benefits of the agrihood from resident and developer perspectives.

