Set to be completed in December 2026, the agrihood will include a diverse portfolio of home prices ranging from the upper $200,000’s to over $500,000 (800–3,100 sq. ft.). Median home values were $435,099 for the agrihood’s zip code in April 2025 (21, 22), demonstrating the agrihood’s commitment to providing affordable options to a diverse range of buyers in this area. Sales for homes began in March 2024 and initial move-in dates are scheduled for fall 2025. Richmond is a diverse, growing city with a racial and ethnic composition of 45.9% Non-Hispanic White, 48.5% Hispanic/Latino, 26.6% Black, and 13.8% Asian (23, 24).

The comparison community is located in Katy, Texas (Harris County), about 23-miles from the agrihood and 36-miles northwest of downtown Houston (25). The comparison neighborhood is a master-planned, non-agriculturally focused development with an estimated 2,824 single-family homes built since 2016 with build-out completion plans set for 2029. It was selected by the research team for its comparable home prices (resale values range between $419,000–$700,000 and new homes start in the $300,000’s) (21, 22) and square footage (83% 1,400–3,000 sq. ft., n = 2,011), zoning (26), and mixture of housing styles and proximity to mixed-use retail, as the agrihood. The comparison neighborhood differs from the agrihood in that its mixed-use retail is more car-dependent and not located within the community, and it is not agriculturally-integrated. However, the comparison neighborhood does have a small community garden containing 13 rentable plots, parks, connecting sidewalks, two amenity centers with physical activity options (e.g., pool, fitness center), ponds, and a prairie-land walking path. Demographically, Katy has a racial and ethnic composition of 57.4% Non-Hispanic White, 30.1% Hispanic/Latino, 12.2% Black, and 7.0% Asian (23, 24).

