##### Comparison participants

Inclusion criteria for comparison participants are: (1) being 18 years or older; and (2) currently living in the comparison neighborhood as their primary or permanent residence at the time of recruitment.

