## Discussion

Consuming a healthy diet and being physically active are crucial for preventing, managing, and improving chronic diseases, yet many communities lack access to fresh foods or safe spaces for physical activity. Neighborhood built environments, particularly those that integrate agricultural production, can be intentionally designed to facilitate walkability, healthy food purchasing, and social interaction. With more than 200 planned or developed agrihoods across the country, a need has been identified for rigorous, longitudinal evaluations to better understand the impact these neighborhoods have on residents’ health and surrounding economies. The present paper details our scalable protocol for a naturalistic study in Fort Bend County, Texas.

By combining two longitudinal cohorts of matched residents, we will address three specific aims with the following expected outcomes based on our team’s experience and formative research. First, from Aim 1 (assessing short-term changes in dietary intake, physical activity, cardiometabolic health indicators, and social connectedness), we expect to demonstrate how physical activity and sedentary behaviors and locations change for adults who relocate to the agrihood compared to adults who do not. We will examine the impact of relocating to the agrihood on MVPA, LMVPA, walking, and sedentary behavior, and expect to find changes in physical activity resource utilization. We expect to explain how living in the agrihood impacts social connection and determine how connection relates to physical activity and healthy eating among participants across time. With this newly generated knowledge, we will be able to more fully explain the dynamic relationship between social connection, built environment, and chronic disease prevention. From exploratory Aim 2 (documenting time use with features of the agrihood and assessing consumer preferences for built and nature design features to provide resident-driven data for future developments), we expect to describe how residents utilize the various features of the agrihood and how much time they spend engaging in these features of their neighborhood. Finally, from exploratory Aim 3 (assessing the economic benefits of the agrihood), we expect to describe resident and developer perspectives of the cost-efficiency of living in and running an agrihood and agrihood farm model.

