Our study design has several strengths, including multiple matched cohorts of residents. In addition, we propose a strong data-driven approach involving biological data collection from the mobile health assessment clinics and device-captured physical activity, along with highly valid and reliable self-report measures that capture individual and community-level preferences and perspectives. Given our multi-disciplinary team and established partnerships with the developers, we anticipate the aims will be achievable, and the results generated from this work will translate into meaningful considerations for residents of these neighborhoods. Moreover, we believe the results will allow us to understand not only how agrihoods affect health and wellbeing, but also how residents engage with them, thereby informing future models for development that are effective for improving health and are economically sustainable.

Given funding and scope of work parameters, this study also has several limitations worth noting. First, the comparison community consists of existing residents, meaning we are unable to capture their baseline prior to moving in, unlike with the agrihood participant sample. Capturing residents as they move into a new development is extremely challenging, and it was not feasible to find a comparison community that was being occupied at the same time as the agrihood. Second, due to budgetary constraints, accelerometer-based physical activity measurement and biological data collection are only feasible among participants in the agrihood community, which may reduce cross-group comparability. Third, the funding support received for this work only covers 13 months, thereby allowing for 6 months of follow-up which may be too short to observe meaningful or sustained behavioral and health changes.

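### The comparison neighborhood is called socio-demographically matched and the cohorts matched, but the only step described is choosing one site on housing and location; no demographic criterion or participant matching supports the label

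*Protocol article*

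**What the plan says.** The label appears in several places. The Abstract (Background) speaks of matched comparison residents. The Introduction calls the site a "geographically and socio-demographically matched non-agriculturally-integrated, master-planned neighborhood". The Discussion opens its summary of aims with "By combining two longitudinal cohorts of matched residents" and then states: "Our study design has several strengths, including multiple matched cohorts of residents". The Abstract and Discussion wording is about people, not places.

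The procedure is in Design and setting. Of the comparison site it says "It was selected by the research team for its comparable home prices", and it adds square footage, zoning, mixture of housing styles and proximity to mixed-use retail. Comparison participants must be adults "currently living in the comparison neighborhood as their primary or permanent residence at the time of recruitment". They are recruited openly, through neighborhood marketing, fairs, door tags and flyers. Data analysis names age, sex and educational attainment as a priori covariates and gives priority to confounders with a baseline standardized mean difference (SMD) above 0.10. It describes no matching or weighting.

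The demographic evidence in Design and setting is one line per city. Richmond (agrihood): "45.9% Non-Hispanic White, 48.5% Hispanic/Latino, 26.6% Black, and 13.8% Asian". Katy (comparison): "57.4% Non-Hispanic White, 30.1% Hispanic/Latino, 12.2% Black, and 7.0% Asian".

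**The concern.** In a non-randomized contrast of two sites, comparability of the groups carries the causal claim. Difference-in-differences removes stable differences in level. It does not remove differences in how groups would have changed anyway. Race/ethnicity, income and housing circumstances can plausibly relate to how activity and diet change over six months. A reader told that the cohorts are matched will discount that threat and credit any divergence to the agrihood.

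This is more than detail left out of a condensed article. The article asserts a design property, and its own eligibility, recruitment and analysis sections do not contain it. The limitations paragraph says that comparison participants are existing residents. It does not say that the cohorts are unmatched, and matching is listed among the strengths just before it.

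**Working it through.** The article states no balance statistic for the two communities, so there is no figure of its own to reproduce. The check has three parts.

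**1. Claim against procedure**

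| Level | What is claimed | What is described |
|---|---|---|
| Neighborhood | Matched geographically and socio-demographically | One site chosen on housing, zoning and retail proximity; no demographic criterion |
| Participants | Matched residents, matched cohorts | Age 18 or over and current residence; open recruitment |
| Analysis | – | Covariate adjustment; no matching or weighting |

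Home price is a partial socioeconomic proxy, and on it the sites are roughly similar. The agrihood runs from the upper $200,000s to over $500,000, with a zip-code median of $435,099. For the comparison, "resale values range between $419,000–$700,000 and new homes start in the $300,000"s. These ranges overlap, so price neither establishes nor refutes a match.

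**2. City race/ethnicity figures (Design and setting)**

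SMD = (p1 − p2) / √{[p1(1 − p1) + p2(1 − p2)] / 2}, with Richmond as p1 and Katy as p2.

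Example, Hispanic/Latino: (0.485 − 0.301) / √[(0.2498 + 0.2104)/2] = 0.184 / 0.480 = 0.38.

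| Category | Richmond | Katy | SMD as printed | SMD rescaled to 100% |
|---|---|---|---|---|
| Non-Hispanic White | 0.459 | 0.574 | −0.23 | −0.41 |
| Hispanic/Latino | 0.485 | 0.301 | 0.38 | 0.17 |
| Black | 0.266 | 0.122 | 0.37 | 0.23 |
| Asian | 0.138 | 0.070 | 0.22 | 0.13 |

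A pooled-proportion SMD and Cohen's h give nearly the same values as the printed column (0.22 to 0.38). The rescaled column divides each percentage by its city total (134.8% and 106.7%). It is only a rough sensitivity check, because it treats the categories as exclusive and complete.

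**3. Do the Richmond figures fit together?**

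Non-Hispanic White plus Hispanic is 45.9 + 48.5 = 94.4%. That leaves at most 100 − 94.4 = 5.6% for all residents who are neither. Yet Black plus Asian is 26.6 + 13.8 = 40.4%. As exclusive categories the four cannot all be right. If the Black and Asian figures include Hispanic residents, then 40.4 − 5.6 = 34.8 of the 48.5 Hispanic percentage points would have to be Black or Asian (fewer if some residents are counted under both), which is hard to credit. Either a label or a figure needs correcting.

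**The case against.** The other side has real force on four points.

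- **Site selection.** A reader might infer that nothing at all was done to make the sites alike. The documents do not support that. In the Introduction the label attaches to the neighborhood, and Design and setting describes purposive selection on housing and price. This supports a claim of similar housing and location. It does not support *socio-demographically*, or *matched* as applied to residents or cohorts.
- **The 0.10 threshold.** A reader might infer that the city differences breach the plan's own imbalance rule. They do not. That rule concerns confounders among participants at baseline, and its consequence is inclusion in the model. City percentages describe neither the 750-home agrihood, nor the comparison development of about 2,824 homes, nor the volunteers. Even with identical populations and 175 per group, the standard error of an SMD is about √(2/175) = 0.107, so |SMD| > 0.10 would arise by chance about 35% of the time for each variable.
- **Scope.** Only four overlapping race/ethnicity categories are available. No age, sex, education or income figures are given for either place, so nothing can be said about demographic characteristics in general.
- **Existing handling.** The plan adjusts for three covariates, has a trigger for others, and discloses the existing-resident limitation. No evidence of differing trends is offered here.

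All four points stand. They narrow the concern to an unsupported label and to adjustment that is left to a trigger. None of them supplies the missing matching.

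**Conclusion.** The matched label is unsupported at participant level, and at neighborhood level it is supported only for housing and location. This follows from the text alone and rests on no assumption.

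The city percentages are at most a warning sign: absolute SMDs of 0.22 to 0.38 as printed and 0.13 to 0.41 rescaled, both conditional on figures that need checking. They cannot serve as evidence for the claim. It would also be wrong to infer from them that the enrolled cohorts will be imbalanced or the estimate biased; that step would need the neighborhoods and enrollees to resemble their cities, and no neighborhood-level figures are given. The point should be corrected. It does not invalidate the design.

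**What to change.** **Wording.** In the Abstract, Introduction and Discussion, replace *matched* with wording such as *comparison neighborhood selected for similar housing and location; participants not matched*. Remove matching from the strengths and state its absence as a limitation.

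**Figures.** Check and correct the city percentages and their labels in Design and setting.

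**Analysis.** In Data analysis, add race/ethnicity and the socioeconomic items among the survey's sociodemographics to the a priori covariates, instead of leaving them to the SMD > 0.10 trigger. Enter each with its interaction with time: stable level differences are already removed by the difference-in-differences, so a main effect alone would do little for the group-by-time estimate. Report participant-level baseline SMDs.

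**Optional.** Propensity overlap weighting can be a sensitivity analysis. It is a method choice that changes the estimand, so it need not replace covariate adjustment. Leave length of residence out of the weights: agrihood cohort members have lived there under three months and comparison participants are existing residents, so there is little overlap by design and weighting cannot repair it.

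**Cost.** The wording costs nothing beyond a less favourable description of the design. The covariates use data already being collected and take a few model degrees of freedom.

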## Materials and methods

### Design and setting

The *Neighborhood & Health Study* employs a quasi-experimental prospective case–control mixed-methods approach. This entails assessing new residents of the agrihood and a comparison group over a period of 6 months (subject to a + 3-month adjustment based on actual move-in date).

The study is primarily situated at Indigo, a new 235-acre, planned 750-home agrihood located in Richmond, Texas (Fort Bend County), about 28 miles southwest of downtown Houston (18). Its developer, Meristem Communities Development Firm, is a Houston-based real estate development firm committed to creating Places for People™ which they envision as being inclusive public spaces (19). Meristem emphasizes resiliency and human-centric design by mindfully and sustainably creating places that connect land, natural systems, and people. For this reason, among others (e.g., proximity to the research team, a development timeline that aligns with the research project timeline, and Meristem’s willingness to partner), Indigo was selected for this study.

The agrihood comprises 42 acres of farm and pasture, over half of the community dedicated to open space, a 12-acre mixed-use town center with a walkable main street design and mixed retail/businesses, a 25-acre lake, integrated trails, “the Filling Station” (welcome center, café, gathering place, farm stand), vehicle-free community areas focused on nature, and spaces for residents to interact and play between rows of houses where there would traditionally be a street. Agriculture in the agrihood will be managed by Agmenity (20), a leader in the local and national agrihood movement, and will include crop fields, orchards, pasture for livestock, year-round production of seasonal produce, farm stand, farm club, agricultural education opportunities, programming, volunteer opportunities, and pastured poultry and egg production. The agrihood was designed to provide a foundational connection to agriculture and a people-first approach that fosters community connection and overall health, while being committed to environmental stewardship.

Set to be completed in December 2026, the agrihood will include a diverse portfolio of home prices ranging from the upper $200,000’s to over $500,000 (800–3,100 sq. ft.). Median home values were $435,099 for the agrihood’s zip code in April 2025 (21, 22), demonstrating the agrihood’s commitment to providing affordable options to a diverse range of buyers in this area. Sales for homes began in March 2024 and initial move-in dates are scheduled for fall 2025. Richmond is a diverse, growing city with a racial and ethnic composition of 45.9% Non-Hispanic White, 48.5% Hispanic/Latino, 26.6% Black, and 13.8% Asian (23, 24).

The comparison community is located in Katy, Texas (Harris County), about 23-miles from the agrihood and 36-miles northwest of downtown Houston (25). The comparison neighborhood is a master-planned, non-agriculturally focused development with an estimated 2,824 single-family homes built since 2016 with build-out completion plans set for 2029. It was selected by the research team for its comparable home prices (resale values range between $419,000–$700,000 and new homes start in the $300,000’s) (21, 22) and square footage (83% 1,400–3,000 sq. ft., n = 2,011), zoning (26), and mixture of housing styles and proximity to mixed-use retail, as the agrihood. The comparison neighborhood differs from the agrihood in that its mixed-use retail is more car-dependent and not located within the community, and it is not agriculturally-integrated. However, the comparison neighborhood does have a small community garden containing 13 rentable plots, parks, connecting sidewalks, two amenity centers with physical activity options (e.g., pool, fitness center), ponds, and a prairie-land walking path. Demographically, Katy has a racial and ethnic composition of 57.4% Non-Hispanic White, 30.1% Hispanic/Latino, 12.2% Black, and 7.0% Asian (23, 24).

